**FIGURE 1 F1:**
[figure not shown]
Visit schedule of enrollment and follow up; * Only collected in the centers where specimen storage is available. # Not required for the prevalent patients X Required. + Optional. RPOMs: patient reported outcome measures, PLA2R: phospholipase A2 receptor.

### Data Collection and Management

The data elements of the personal domain (demographics, medical history, Chinese medicine specific information including symptoms and tongue images, etc.), the exposure domain (treatment prescriptions of CHM and conventional drugs), and the outcome domain will be recorded. Each participant will have a unique number, and their personally identifiable information will not be collected. Both spot urine specimen and 24 h urine specimen will be collected to assay for red blood cells, white blood cells, urinary protein-to-creatinine ratio, and 24 h total urinary protein. Fasting blood draw will be tested for complete blood cells (red blood cell, hemoglobin, white blood cell, neutrophil, leukomonocyte, and platelets), metabolic panel (blood glucose, potassium, albumin, aspartate aminotransferase, alanine aminotransferase, uric acid, creatinine, total cholesterol, triglycerides, and low-density lipoprotein), and PLA2R. GFR will be estimated using the 2009 Chronic Kidney disease Epidemiology Collaboration (CKD-EPI) equation based on serum creatinine (Levey et al., 2009). Recently, a new equation based on both serum creatinine and cystatin C, which is also proposed by CKD-EPI, will be used to estimate GFR as well (Inker et al., 2021). Patient report outcome measures including the Kidney disease Quality of Life-36 which will be used to assess quality of life. At the baseline and each annual visit, a blood sample and a urine sample will be collected for cryopreservation, which will be used for detection of disease specific biomarkers in further research phases. Additionally, if participants are newly diagnosed by kidney biopsy, the kidney biopsy tissue will be cryopreserved as well. The scheduled time points for data collection are summarised in Figure 1.

The data of the core Chinese medicine syndrome of dampness in IMN will be collected by using the validated Dampness Syndrome Scale (Lu et al., 2021) and the tongue image acquisition system. The scale consists of 30 items. There are five options for each item from 0 to 4 which indicate no symptoms, mild, moderate, heavy, and very heavy symptoms. The total score ranges from 0 to 120. More than 15 items with at least one point can be defined as dampness syndrome. The higher the score, the more severe the dampness syndrome. Tongue images will be captured by using a smartphone tongue image acquisition application with a standard color correction chart (Figure 2) and quantified the tongue characteristic by using a computerized tongue image analysis system (Shanghai Daosh Medical Technology Co., Ltd.). (ISO, 2019; ISO/TS, 2020).

**FIGURE 2 F2:**
[figure not shown]
Tongue image capture by using a smart phone application; includes a demonstration of training; **(A)** interface of the tongue image acquisition application, including a tongue image area and a color correction chart area; **(B)** standardized operation for sticking tongue out and position of a standard color correction chart; **(C)** take photo with the tongue image acquisition application in a smart phone. *Note: The person depicted is not a patient and was taken with the participant’s knowledge.

All data will be collected and recorded using electronic data collection (EDC). A systematic training is required for the personnel in all participating sites before the commencement of recruitment.

### Outcomes

The primary outcome is clinical composite remission at 24 months after enrollment. Composite remission is defined as either complete remission (CR) or partial remission (PR). Secondary outcomes are CR, PR, time to remission (CR, PR, and CR or PR), no response, relapse, urine protein excretion, urinary protein creatinine ratio, serum albumin, annual change of GFR (GFR slope), PLA2R, adverse events, and composite endpoint of 40% reduction of GFR, doubling of serum creatinine, end-stage renal disease (ESRD), and death. The outcome variables and definitions are presented in Table 1.

**TABLE 1 T1:** Outcome variables and definitions.

Outcome variables	Definitions
Primary outcome	
Composite remission	Either complete remission or partial remission
Secondary outcomes	
Complete remission (CR)	A reduction of proteinuria to ≤0.3g/24 h accompanied by a normal serum albumin and a normal Scr. Beck et al. (2013)
Partial remission (PR)	At least 50% reduction from peak value of proteinuria to a level between 0.3 and 3.5 g/24 h, accompanied by an improvement or normalization of serum albumin and a stable Scr. Beck et al. (2013)
Relapse	The development of proteinuria ≥3.5 g/24 h after a CR or PR
Time to complete remission	Days from enrollment to CR
Time to partial remission	Days from enrollment to PR
No response	No reduction in proteinuria of at least 25% from baseline
Serum albumin	/
Urine protein excretion	Urine protein excretion within 24 h
Urinary protein-to-creatinine ratio (UPCR)	/
Antibodies against PLA2R	/
Doubling of serum creatinine	Doubling increase of serum creatinine from baseline
40% reduction of eGFR	A reduction in eGFR of 40% from baseline. Serum creatinine based eGFR is calculated using the Chronic Kidney disease Epidemiology Collaboration (CKD-EPI) equation
End-stage renal disease (ESRD)	eGFR ≤15 ml/min/1.73m^2^ or commencement of renal replacement treatment
Composite endpoint	ESRD or 40% reduction of eGFR or doubling of serum creatinine
eGFR slope	Annual change in eGFR

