### Eligibility Criteria

Eligible candidates for the study are IMN patients of any risk levels to capture a broad spectrum of clinical presentations. Inclusion criteria include Chinese adults aged from 18 to 85 years old; diagnosis of biopsy-proven IMN or antibodies against phospholipase A2 receptor (PLA2R)-positive patients who are not associated with other diseases which cause secondary MN, such as systemic lupus erythematous, infections with hepatitis B virus, hepatitis C virus, or syphilis, sarcoidosis, and cancer. Patients with the following criteria will be excluded: patients with a GFR less than 15 ml/min/1.73 m^2^; patients with comorbidities including malignant cancers, decompensated cirrhosis, hematologic diseases, and mental diseases.

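### The CR and PR definitions leave a gap below 0.3 g/24 h: some patients fail the primary outcome at 0.2 g who would succeed at 0.5 g

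*Protocol article*

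**What the plan says.** The Outcomes section of the protocol article states: "The primary outcome is clinical composite remission at 24 months after enrollment". Composite remission is CR or PR, and no third route to success is given.

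Table 1 sets the components:

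- CR: no more than 0.3 g/24 h of proteinuria, "accompanied by a normal serum albumin and a normal Scr".
- PR, proteinuria condition: "At least 50% reduction from peak value of proteinuria to a level between 0.3 and 3.5 g/24 h".
- PR, laboratory conditions: "accompanied by an improvement or normalization of serum albumin and a stable Scr".
- No response, a secondary outcome: "No reduction in proteinuria of at least 25% from baseline".

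On kidney function, Eligibility Criteria excludes only "patients with a GFR less than 15" (units ml/min/1.73 m²), so patients with raised creatinine at entry are admitted. The Enrollment and Follow-Up section admits prevalent, already treated patients as well as incident ones, and the Abstract sets no minimum proteinuria. The Statistical Plan analyses composite remission, CR, PR and no response as separate outcomes, each by chi-square test and logistic regression.

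**The concern.** CR is meant to be the deeper response and PR the shallower one. CR therefore has the stricter laboratory conditions: normal albumin and normal creatinine, against improved albumin and stable creatinine for PR. PR also carries a lower proteinuria bound, which separates it from CR. Together these leave a region that belongs to neither category: proteinuria below 0.3 g/24 h, PR's other conditions met, but creatinine or albumin not normal.

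Two kinds of patient fall there. One has chronically raised but stable creatinine, which the eligibility criteria permit. The other has an albumin that has improved but is not yet normal. Because the primary outcome is read at 24 months, a patient in PR at 0.4 g who improves to 0.2 g with the same laboratory status turns from success to failure. Time to remission, and relapse (which presupposes an earlier CR or PR), use the same definitions.

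At stake is the validity of the primary endpoint for these patients, and a recorded remission rate that is too low by their share of the cohort.

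**Working it through.** The plan gives no figure to reproduce here; the check is of the logic of the definitions. The rules come from Table 1. The proteinuria values are illustrative assumptions, because the document gives no distribution.

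Let P be 24-month proteinuria (g/24 h), K the peak and B the baseline.

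- CR: P ≤ 0.3, albumin normal, creatinine normal.
- PR: 1 − P/K ≥ 0.50, P between 0.3 and 3.5, albumin improved or normal, creatinine stable.
- Composite: CR or PR.
- No response: 1 − P/B < 0.25.

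**The gap.** Take K = 8, B = 6, albumin normal, creatinine abnormal but stable, and vary only P.

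| P | Fall from peak | CR | PR | Primary outcome |
|---|---|---|---|---|
| 0.5 | 1 − 0.5/8 = 93.8% | no (P, creatinine) | yes | success |
| 0.3 | 1 − 0.3/8 = 96.3% | no (creatinine) | only if the bound is included | unclear |
| 0.2 | 1 − 0.2/8 = 97.5% | no (creatinine) | no (below 0.3) | failure |

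With normal creatinine and an albumin that is improved but not normal, the rows give the same results, with albumin in place of creatinine as the CR condition that fails. For these patients the endpoint is not monotone in proteinuria: a better value scores worse.

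**Effect on the rates.** Let T be the remission rate in a group if gap patients counted as remitters, and q the proportion of the group in the gap. The recorded rate is T − q. For two groups, the recorded difference is (T₁ − T₂) − (q₁ − q₂). The level is understated by q in each group, while the contrast moves only by q₁ − q₂. The document gives neither q nor the inputs needed to estimate it.

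**The overlap (secondary outcome only).** Take K = 8, B = 3.0, P = 2.8, with albumin improved and creatinine stable.

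- Fall from peak: 1 − 2.8/8 = 65%, and 2.8 lies within 0.3 to 3.5, so PR is met.
- Fall from baseline: 1 − 2.8/3.0 = 6.7%, below 25%, so no response is met as well.

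Within the PR range, both hold whenever 0.75B < P ≤ 0.5K. That requires B < (2/3)K. If peak and baseline were the same value it could not occur, because 0.75B exceeds 0.5B. The article does not equate them, and a prevalent patient's peak may well precede enrolment. CR and no response can also coincide: with B = 0.30 and P = 0.25 the fall is 1 − 0.25/0.30 = 16.7%.

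**The case against.** **The definitions come from a cited source, and an article leaves detail to the full plan.** Table 1 cites a source for CR and PR, and departing from it has a price in comparability. That stands, and it is a reason to keep the literal definition as a sensitivity analysis. It does not remove the problem: the article itself fixes these conditions for its primary outcome, and applying them as written produces the gap.

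**The treatment comparison is already protected.** The propensity score includes baseline eGFR, proteinuria and serum albumin. Balance is checked at |d| > 0.10, weighting is used as a robustness check, and the Cox model also adjusts for GFR. This stands as a limit on between-group bias. It does not recode a patient at 0.2 g, nor restore the recorded remission rate. Gap membership also depends on creatinine and albumin at 24 months, which baseline covariates predict only in part.

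**Readings that go too far.** A reader might set the share of patients miscoded against the planning difference of 73.7% − 67.0% = 6.7 points and infer that the comparison could be overturned. The document does not support this. It gives no basis for the share, and a share of the whole cohort is a different quantity from a between-group difference: an equal share in both groups leaves the absolute difference unchanged.

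A reader might also infer that every patient at or below 0.3 g with stable creatinine is wrongly failed. That is too broad. A patient with peak 0.5 g now at 0.28 g has fallen 1 − 0.28/0.5 = 44% and fails PR's own halving condition. A patient whose albumin is neither improved nor normal fails its albumin condition. Neither failure comes from the gap.

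Finally, the overlap with no response might be read as a defect of the primary outcome. It is not: no response is secondary and tested separately, and nothing in the article says the categories are mutually exclusive.

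**Conclusion.** The gap is real and affects the primary outcome. Below 0.3 g/24 h, a patient who has at least halved from peak and meets PR's albumin and creatinine conditions, but does not have both values normal, is coded as a failure, although the same patient at 0.5 g is coded as a success. At exactly 0.3 g the text is ambiguous.

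The conclusion rests only on the wording of Table 1 and on eligibility that admits patients with abnormal creatinine. It involves no judgement on which clinical threshold is right. Its frequency cannot be derived from the document. The direction for the overall remission rate is clear (too low); for the treatment contrast, neither direction nor size can be stated. The definitions should be reconciled before outcomes are derived, particularly because the registry is unblinded and an ad hoc choice made after seeing the data would be hard to defend.

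The overlap between PR and no response is a minor clarification to a secondary outcome.

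**What to change.** Reconcile the CR and PR rows of Table 1 so that a patient who meets every other PR condition is not excluded from composite remission for having proteinuria below PR's lower bound. One way is to read PR as including such patients whenever CR is not met. The halving from peak and the albumin and creatinine conditions stay as they are. This also settles the case of exactly 0.3 g.

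Keep the literal Table 1 definition as a sensitivity analysis, for comparability with the cited source, and report how many patients change category. That count gives the size that cannot be known now.

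For the secondary outcome, count no response only among patients not in CR or PR.

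The cost is a few words in Table 1, the matching lines of the derivation program and one added sensitivity analysis. No new data are needed. As a change to outcomes, the Ethics and Dissemination section requires it to go to the ethics committee and then into the registry record.

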## Abstract

**Introduction:** Some encouraging findings of Chinese herbal medicine (CHM) in management of idiopathic membranous nephropathy (IMN) obtained in the setting of clinical trials are hard to validate in the daily clinical practice due to a complicated treatment scenario of CHM in practice. The primary objective of this registry is to provide a description of treatment patterns used in management of IMN and assess clinical remission in daily practice in a Chinese population sample with IMN.

**Methods and analysis:** This is a prospective, multicenter cohort which will comprise 2000 adults with IMN regardless of urinary protein levels that will be recruited from 11 nephrology centers across China. The participants will be followed for up to at least 2 years. Primary outcome is composite remission (either complete remission or partial remission) 24 months after enrolment. The secondary outcomes are complete remission, partial remission, time to remission, no response, relapse, proteinuria, annual change of glomerular filtration rate, antibodies against PLA2R, and composite endpoint of 40% reduction of glomerular filtration rate, doubling of serum creatinine, end-stage renal disease, and death. Propensity score analysis will be used for matching and adjustment.

**Ethics and dissemination:** This study has been approved by the Ethics Committee of Guangdong Provincial Hospital of Chinese Medicine (BF2020-094-01). Results of the study will be published in both national and international peer-reviewed journals, and presented at scientific conferences. Investigators will inform the participants as well as other IMN patients of the findings via health education.

**Study registration**: ChiCTR2000033680 (prospectively registered).

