## Introduction

Membranous nephropathy (MN) is an autoimmune disease that affects the kidney glomerulus. It is the leading cause of nephrotic syndrome in nondiabetic adults, counting for 20–37% in most ages and up to 40% in patients over 60 (Ronco and Debiec, 2015; Couser, 2017). The incidence of MN is 10–12 per million persons per year in Europe and the USA, (Maisonneuve et al., 2000), and a rising incidence has been reported in China (Zhang et al., 2017). Approximately 80% of the cases are idiopathic and 20% of them are pathogenically associated with other systematic diseases (i.e., secondary MN). Optimal supportive care and therapy are applied to all patients with idiopathic MN (IMN) (Floege et al., 2019). Immunosuppressive therapy is recommended for IMN patients at risk for progressive kidney injury (e.g. decreasing glomerular filtration rate [GFR]) or with severe life-threatening nephrotic syndrome (Floege et al., 2019). Glucocorticoids combined with cyclophosphamide or calcineurin inhibitors, as well as rituximab, are the major treatment regimens for IMN patients at different risks. They are effective and also accompanied with risks including toxic effects and a high incidence of relapse. For rituximab, the high cost is a large obstacle to acceptability for patients. Other medicines, such as botanicals which include Chinese herbal medicine (CHM), are also widely used in treating IMN in China (Xu et al., 2015).

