### Enrollment and Follow-Up

This study is designed to be a long-term longitudinally extensible cohort. The study aims to include 2000 Chinese IMN adults. The recruitment is estimated to take 42 months, from July 2020 until December 2023. The patients who meet the inclusion criteria will be enrolled continuously. Both incident patients and prevalent patients will be recruited by physicians in nephrology clinics and inpatient departments in 11 participating sites. Incident patients are individuals who are newly diagnosed and first initiated on treatments. Prevalent patients are individuals who have already been diagnosed as IMN and have been receiving treatments before the study. Meanwhile, the electronic medical record in 11 participating sites will be retrospectively screened to recruit the confirmed cases.

Individuals who are eligible and consent to participate will be invited to attend a baseline visit. Participants will be followed for up to at least 2 years. Participants who experience the primary endpoint (remission) will be continued to be followed up until the end of the study or death. The schedule of follow-up visits is presented in Figure 1. Follow-up visits will occur quarterly in the first year after enrollment and then semi-annually from the second year. The baseline, semi-annual, and annual follow-up visits in the first year and annual visits from the second year are required in-person visits. All other visits can be in-person or remote via telephone call or smartphone applications. In order to retain participants and minimize the number of dropouts and withdraws as well as the missing data, a reasonably flexible visit time window within a range of 4 weeks forward or backward from the scheduled visit day will be acceptable.

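### Relapse is one absolute threshold (≥3.5 g/24 h) in a cohort with no proteinuria floor, so remitters whose peak was below 3.5 g/24 h can lose their whole response without counting as relapsed

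*Protocol article*

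**What the plan says.** All references are to the protocol article.

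- **Relapse** (Outcomes, Table 1): "The development of proteinuria ≥3.5 g/24 h after a CR or PR". No other rule is given for patients whose disease never reached that level.
- **Partial remission** (same table), proteinuria part: "At least 50% reduction from peak value of proteinuria to a level between 0.3 and 3.5 g/24 h". This is judged against the patient's own peak, with no minimum peak.
- **Complete remission** (same table): "A reduction of proteinuria to ≤0.3g/24 h accompanied by a normal serum albumin and a normal Scr". Again there is no minimum starting level.
- **Entry**: the Abstract describes "adults with IMN regardless of urinary protein levels", and Eligibility Criteria states "Eligible candidates for the study are IMN patients of any risk levels to capture a broad spectrum of clinical presentations". No inclusion or exclusion criterion concerns proteinuria.
- **Newly treated and already treated patients** (Enrollment and Follow-Up): "Both incident patients and prevalent patients will be recruited by physicians in nephrology clinics and inpatient departments in 11 participating sites".
- **Analysis** (Statistical Plan): relapse is compared by chi-square test and logistic regression, with no stated restriction by peak or baseline proteinuria. The propensity model lists proteinuria, eGFR, serum albumin and PLA2R antibody level among its variables. It does not list peak proteinuria. Planned subgroups include incident versus prevalent patients and risk of progressive loss of kidney function.

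**The concern.** Remission is open to patients at every level of disease, and PR is scaled to the patient's own peak. Relapse is not scaled: it is a single nephrotic-range level. That fits a cohort in which everyone has at some time been at or above 3.5 g/24 h, and this cohort is deliberately wider.

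Patients with a lower peak can enter, remit and join the relapse denominator, but returning to where they started does not make them an event. Two things are at stake. First, a registry meant to describe what happens in daily practice would report a relapse rate that misses part of the lost response. Second, the rate in any treatment group would depend partly on how many of its remitters ever had a peak high enough for a full return to count. The Introduction gives the outcome some weight, since it describes conventional regimens as "effective and also accompanied with risks including toxic effects and a high incidence of relapse".

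**Working it through.** **Inputs.** From Table 1: CR needs ≤0.3 g/24 h; PR needs ≤50% of peak and a value between 0.3 and 3.5 g/24 h; relapse needs ≥3.5 g/24 h. The albumin and creatinine conditions are taken as met. The article gives no relapse rate and no distribution of peak proteinuria, so there is no figure of the plan to reproduce.

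**Step 1: full return to peak.** Hypothetical patients fall to 45% of peak and then return to it. The last column is 3.5 ÷ peak.

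| Peak (g/24 h) | 45% of peak | PR rule met | Return to peak is a relapse | Multiple of own peak needed |
|---|---|---|---|---|
| 1.0 | 0.45 | yes | no | 3.50 |
| 2.0 | 0.90 | yes | no | 1.75 |
| 3.0 | 1.35 | yes | no | 1.17 |
| 3.4 | 1.53 | yes | no | 1.03 |
| 3.5 | 1.58 | yes | yes | 1.00 |
| 5.0 | 2.25 | yes | yes | 0.70 |

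The gap covers every peak below 3.5 g/24 h. These patients can be counted, but only by becoming worse than they have ever been.

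**Step 2: the other end of the scale.** A patient with peak 8 g who reaches 3.3 g is in PR, since (8 − 3.3) ÷ 8 = 59% reduction, and relapses after a rise of 0.2 g. A patient with peak 3.0 g in PR at 1.35 g can rise by 1.65 g, back to peak, and not relapse.

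**Step 3: what matching sees.** Take two prevalent patients, both enrolled at 2 g/24 h, one with an earlier peak of 8 g and one who never exceeded 2 g. On proteinuria they are identical to the propensity model. A return to peak is a relapse only in the first. For incident patients, enrolment proteinuria is plausibly close to the pre-treatment peak, so matching does more.

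**Step 4: possible size, on assumed figures only.** Let L be the true proportion of remitters who lose their response and s the share of remitters with a peak below 3.5 g/24 h. Assume L does not depend on peak, lost responses in the higher-peak patients all reach 3.5 g, and those in the lower-peak patients never do. Then recorded relapse = L × (1 − s). With L = 30%:

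- s = 15%: 0.30 × 0.85 = 25.5%
- s = 25%: 0.30 × 0.75 = 22.5%
- s = 30%: 0.30 × 0.70 = 21.0%
- s = 40%: 0.30 × 0.60 = 18.0%

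Equal s in both groups gives an odds ratio of 1, with both rates too low. For s of 30% against 25% the odds ratio is (0.21/0.79) ÷ (0.225/0.775) = 0.92. For 40% against 15% it is (0.18/0.82) ÷ (0.255/0.745) = 0.64. With the groups exchanged, these become 1.09 and 1.56. Nothing in the article fixes s in either group.

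**The case against.** The strongest defence is that keeping the word relapse for nephrotic-range recurrence is clear and reproducible, and that 3.5 g/24 h matches the upper limit of PR. The lost response is not hidden either: 24-hour protein excretion and the protein-to-creatinine ratio are separate outcomes. If the primary outcome is read as status at 24 months, a patient with peak 3.0 g who is back at 3.0 g no longer meets PR. All of this stands, and it keeps the point to one secondary outcome. It does not explain why patients who must exceed their own worst value in order to count sit in the same denominator as those who need not.

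A second defence is that baseline proteinuria, albumin, eGFR and antibody level are in the propensity model, with balance checks, inverse probability weighting as a robustness check, and incident/prevalent and risk-level subgroups. This stands in good part for incident patients. It is weaker for prevalent patients, and the subgroups leave the definition unchanged.

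A third is that at-risk sets are often left to an analysis plan that is not shown. That would answer a missing detail; here the definition is stated in full and does not fit the stated population.

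A reader might go further and infer that the rule favours Chinese herbal medicine (CHM), because the Introduction directs immunosuppression to patients at risk of progression or with severe nephrotic syndrome. The article does not support that. The Statistical Plan matches anyone exposed to CHM with patients on conventional drugs alone, so combination users fall on the CHM side. The Introduction also says supportive care goes to all patients, so milder cases can be in the comparator, and it cites CHM use in patients with nephrotic-range proteinuria. The 40% against 15% split behind the odds ratio of 0.64 is an assumption, and an unmatched one.

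**Conclusion.** The mismatch holds on the text. A remitter with a peak below 3.5 g/24 h can return fully to the earlier level, remain in the denominator and not be counted as relapsed. The overall relapse rate is therefore understated as a measure of lost response, and the same label describes different events at different peaks.

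A distorted regimen comparison is possible, in either direction, if the share of such remitters differs between groups after matching; the risk is greater among prevalent patients. Size and direction cannot be computed from the document, and the odds ratios above only show how the result moves with assumed shares. A bias towards CHM is not established. The primary outcome is not affected by this rule. This is worth correcting before analysis, as a moderate point on a secondary outcome.

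**What to change.** In Table 1 and in the analysis of relapse, state that the at-risk set for relapse as defined is remitters whose peak proteinuria was ≥3.5 g/24 h. Alternatively, keep all remitters and report relapse separately for peak below 3.5 and peak ≥3.5 g/24 h. Use the same peak value that PR is judged against.

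For all remitters, add a supportive outcome, loss of remission: the study's own CR or PR proteinuria criteria are no longer met at a later visit. It should not become the main regimen comparison.

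The cost is wording; no new data item is needed, because PR already requires the peak. There are two downsides. The restricted relapse analysis has fewer patients. The supportive measure reacts to small changes near its threshold: with peak 3.0 g the PR limit is 1.5 g, so a patient at 1.45 g loses remission at 1.55 g, a rise of 0.1 g. Confining it to the proteinuria criteria at least avoids triggering on albumin or creatinine alone.
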